### Sample size determination

The minimum sample size required to test the proposed study hypotheses has been determined using the formula for comparing two proportions in selected samples of both intervention and control groups [57]. This formula gave the required number (n) for each group. This provided a total sample size of 196 participants in each group, which will then be multiplied by two since the study is comprised of two arms. Therefore, 392 are the calculated sample size required to test the hypothesis for this study *(Refer to S1 File).*

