### Study process

An illustration of the study process was done in accordance with CONSORT statement [55]. During the eight weeks recruitment period, a total of 551 pregnant women had been assessed for possible inclusion in the study out of which 159 did not meet the inclusion criteria while ten declined to participate. The remaining three hundred and eighty-two participants were then randomly assigned equally, to either the intervention or the control group. SPIRIT schedule of the study and flow diagram of the study are shown in Figs 1 and 2 respectively. The baseline data of the study participants has been taken and they will both be followed up at 6 weeks post-delivery, 10 weeks post-delivery and 14 weeks post-delivery to assess the effect of the intervention regarding their knowledge, attitude, outcome expectations, self-efficacy, cultural beliefs and assumptions of religious regulations towards child immunization, as well as to assess their child immunization uptake.

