In order to determine within-group differences with time for knowledge scores, attitude scores, outcome expectation scores, self-efficacy scores, cultural beliefs scores and assumptions of religious regulations scores the researcher will conduct one-way repeated measures analysis of variance (ANOVA) for these variables if there is no substantial non-normality of the residuals. Intention-to-treat analysis (ITT) will be carried-out separately for each group and replacement of missing data will be done through using multiple imputations technique. The estimated outputs that will be obtained after ITT analysis will then be pooled into a single data set, after that, the Generalized Linear Mixed Models (GLMM) analysis will be carried-out to investigate the overall effectiveness of the intervention using 95% Confidence Interval (CI) and 0.05 will be set as the level of significance. Two measures of effect size will be used in this study: Partial Eta squared and the coefficients of the fixed effects. Partial Eta squared will be used in the mixed design repeated measures ANOVA, and will be classified as small, medium or large effect (0.2, 0.5 and 0.8) respectively according to the magnitude. The coefficients of the fixed effects will be used in the GLMM analysis.

In order to check the robustness of the result, sensitivity analysis will be performed to determine the effect of drop out and non-response on the findings of the proposed study, the GLMM analysis will be repeated again without replacing the missing values. The differences between the coefficients obtained after replacement (intention to treat analysis) and before replacement of the missing values (per-protocol) will then be calculated and expressed as percentages of the former.

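### The sensitivity analysis labelled per-protocol is an available-case analysis, and its agreement with the imputed result cannot show robustness to informative drop-out

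*Protocol article*

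**What the plan says.** All of this stands in the protocol article, Data analyses.

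- Main analysis: "Intention-to-treat analysis (ITT) will be carried-out separately for each group", and "replacement of missing data will be done through using multiple imputations technique". A GLMM then estimates the overall effect, with the fixed-effect coefficients as its effect measure and "0.05 will be set as the level of significance".
- Purpose of the second analysis: "sensitivity analysis will be performed to determine the effect of drop out and non-response on the findings of the proposed study".
- What it consists of: "the GLMM analysis will be repeated again without replacing the missing values".
- Its label and metric: the differences between the imputed coefficients and those obtained "before replacement of the missing values (per-protocol) will then be calculated and expressed as percentages of the former".

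The article thus equates intention to treat with imputed data and per-protocol with non-imputed data. No section ties the second analysis to attendance at the five modules, receipt of reminder calls or any other measure of adherence.

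**The concern.** Two separate conclusions could be drawn from a small percentage difference, and neither would be supported.

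The first is that the intention-to-treat and per-protocol results agree. A per-protocol set is defined by what participants received. Here a woman who attended no module but has outcome data stays in, while a woman who attended all five and was then lost contributes little or nothing.

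The second is that drop-out does not affect the result. Both analyses are valid if missingness depends only on observed data, and both can be wrong in the same direction if it does not.

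The article's own procedures make outcome-dependent missingness plausible. Under Study pro forma, uptake is recorded on a card that the mother holds and hands in once the third Penta dose has been given, so card return is linked to completion. Under Intervention, only the intervention arm gets reminder calls before each immunisation date, so return among mothers who do not complete may differ by arm. That is the pattern that biases a between-arm coefficient.

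**Working it through.** The plan states no figure for this point, so there is none to reproduce. The check has three parts.

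**1. What separates the two analyses**

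| Feature | Main analysis | Analysis called per-protocol |
|---|---|---|
| Model | GLMM | Same GLMM |
| Missing values | Multiply imputed | Not replaced |
| Adherence restriction | None stated | None stated |

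Imputation is the only stated difference.

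**2. Whether the metric can signal informative drop-out**

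An illustrative simulation used 191 per arm (382 randomised, divided by 2, from Study process), a continuous score at baseline and three follow-up visits, a true effect of 0.5, about 22% missing at the last visit, and 300 replicates. Everything except the 191 and the visit structure is assumed. It compared imputation by arm with a likelihood-type estimate from the observed data.

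| Mechanism | Full data | Imputed | Not imputed | Difference, % of imputed |
|---|---|---|---|---|
| Missing at random | 0.515 | 0.513 | 0.511 | 0.3% |
| Low scorers in the intervention arm drop out more | 0.518 | 0.660 | 0.659 | 0.1% |

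In the second row both estimates overstate the full-data effect by about 27% (0.660/0.518 = 1.27), yet the planned percentage difference is close to zero.

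**3. What this could mean for uptake**

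Inputs:
- True uptake is 33% v 20%, the third-dose DPT figures of the Sokoto trial quoted in the Background, used here only as an example.
- Return is 95% for completers in both arms and 60% for control non-completers (assumed).
- Return for intervention non-completers is varied (assumed).
- A logit link is assumed; the article does not state the link.

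True odds ratio = (0.33/0.67)/(0.20/0.80) = 0.4925/0.25 = 1.970.

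Observed odds in an arm = (uptake × return of completers)/((1 − uptake) × return of non-completers).

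Control: (0.20 × 0.95)/(0.80 × 0.60) = 0.190/0.480 = 0.3958, an observed proportion of 0.190/0.670 = 28.4%.

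| Return of intervention non-completers | Observed odds, intervention | Observed proportion | Observed odds ratio |
|---|---|---|---|
| 60% | 0.3135/0.4020 = 0.7799 | 43.8% | 1.970 |
| 75% | 0.3135/0.5025 = 0.6239 | 38.4% | 1.58 |
| 45% | 0.3135/0.3015 = 1.0398 | 51.0% | 2.63 |

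On the log-odds scale the true coefficient is ln 1.970 = 0.678. At 75% it becomes ln 1.576 = 0.455, which is 33% lower. At 45% it becomes ln 2.627 = 0.966, which is 42% higher. Imputing within each arm from the observed outcomes fills the gaps at about the observed proportion, so it returns the same odds ratio and the planned comparison shows nothing.

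Counting no record as not immunised gives 31.35% v 19.0% in all three rows, because completers' return is held at 95%: (0.3135/0.6865)/(0.190/0.810) = 1.947. In the 75% and 45% rows that analysis would differ from the planned ones and so would flag a problem. It would itself be biased if completers' return differed by arm.

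The losses implied are large: 33% in control (1 − 0.670), and 18.4% or 38.5% in the intervention arm (1 − 0.816, 1 − 0.615).

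**The case against.** **Equal return by arm.** A reader might take 33% v 20% appearing as 43.8% v 28.4% as proof that the planned effect is biased. It is not. When return depends on outcome equally in both arms, the odds ratio stays at 1.970, so a logit coefficient has no error for the comparison to miss. Only the proportions and the risk difference shift (13.0 to 15.5 points). In that setting, counting no record as not immunised gives 1.947, slightly further from the truth than the planned analysis. This objection stands in full: the concern about uptake depends on return differing by arm given outcome.

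**The comparison is not useless.** The article says it wants the effect of drop-out and non-response; it does not claim to test missing at random. The two results can differ if the 14 adjusting variables named in the abstract have item non-response, if imputation uses auxiliary variables, or if the imputation model is poor. That stands. To say that the comparison is no check on drop-out at all would go too far.

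**Detail left to the analysis plan.** Delta-shift analyses and per-protocol definitions are often specified there, so their absence from a journal article is no fault. That also stands. What remains is what the article does state: a wrong label, and a comparison of two analyses with a shared assumption offered as the robustness check.

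**Missing uptake may be small.** Eligible mothers intend to use this hospital's immunisation clinic, so lost cards might be filled from clinic records. The article does not say that this will be done.

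**Conclusion.** The point holds in limited form.

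The label is wrong on the face of the text: with no adherence criterion, the analysis is available-case. That all randomised women enter it is an inference from the absence of any stated restriction.

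A small percentage difference between coefficients cannot support a claim of robustness to informative drop-out. This rests on imputation and the GLMM sharing essentially the same missing-at-random assumption, which is usual but is not named in the article.

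The size cannot be known from the document. Under the assumed return rates, a true odds ratio of 1.97 would be seen as 1.58 or 2.63, depending on whether intervention non-completers return more or less often than control ones. The direction is therefore also unknown.

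A reader might infer that the main analysis is invalid or that the trial's estimate is biased. The documents do not support either: this is a secondary robustness analysis, the main estimate is untouched by its label, and no drop-out data are reported.

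**What to change.** - Rename the non-imputed GLMM available-case, and do not report it as per-protocol or as proof of robustness to drop-out. It can stay as a check on item non-response and on the imputation model.
- For uptake, add a delta-shift analysis: move the imputed log-odds by an arm-specific amount until the conclusion changes, and report how large that shift is.
- Add one further scenario in which no vaccination record counts as not immunised in both arms. It should not be the only one, since it assumes that completers' records are equally complete in both arms.
- Report a per-protocol estimate only if module attendance is recorded, and define the set by it. The article does not say that attendance is recorded, so this needs confirming first.

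The cost is wording and a few extra model runs. The Study process section describes baseline as complete and follow-up as still to come, so the change can precede the outcome analysis, using the route under Protocol amendments.

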## Discussion

To our knowledge, this will be the first immunisation health education intervention (RCT) to be conducted with application of health theory targeting antenatal mothers. The first study was a controlled community trial conducted in Sokoto State, Nigeria which focused on evaluating the impact of immunisation health education intervention using Community Level Nutrition Information System for Action (COLINSA) strategy on knowledge and practice of childhood immunization among mothers. At the end of the study, the proportion of children in the intervention group who received DPT1 was 35% and DPT3 33% while in the control group DPT1 was 25% and DPT3 was 20% [53]. The second study which was a randomised controlled trial, was carried-out to evaluate the effect of a low-literacy immunisation promotion educational intervention in improving DPT/Hepatitis B vaccine uptakes among 366 mother-infant pairs with infants aged ≤6 weeks of age in Karachi, Pakistan. At four months after enrolment, among 179 mother-infant pairs in the intervention group, 129 (72.1%) had received all 3 doses of DPT/Hepatitis B vaccine while in the control group only 92/178 (51.7%) received the all 3 doses [54]. Social cognitive theory (SCT) is one of the health theories commonly used in health education interventions [64, 65] which describes human behaviour through the influence of personal and environmental factors [60]. The theory accounts for human behaviour, cognition and environment and is the only health theory that takes into account reciprocal interaction, unlike other theories such as Information Motivation Behavioural Skills model [64, 66]. Many personal and environmental factors have been found to influence childhood immunisation uptake in African countries including Nigeria. Therefore, using SCT may enable researchers to address both personal and environmental factors influencing childhood immunisation uptake. Our study will ensure maternal knowledge, attitude, outcome expectations, self-efficacy, cultural beliefs and assumptions of religious regulations regarding childhood immunization uptake are increased at the end of the intervention. The study findings will be communicated to participants, healthcare professionals, the public, and other relevant groups via publication.

### Protocol amendments

Any important protocol modifications for-instance, changes in the eligibility criteria, outcomes or analysis will be communicated to Pan African Clinical Trials Registry and Jawatankuasa Etika Universiti Putra Malaysia.

## Abbreviations

VPDs: Vaccine Preventable Diseases
EPI: Expanded Programme on Immunization
SCT: Social Cognitive Theory
